### Intervention

Intervention participants follow a fully defined diet-physical activity program designed to create a weekly negative energy balance equivalent to 3500 kcal, after adjustments for metabolic adaptations that occur during extended periods of weight loss. The intervention groups (135 participants in each arm) receive the same physical activity protocol promoting published physical activity guidelines and translated into step recommendations [67,68], but one of two dietary patterns: low fat or low carbohydrate.

### Dietary Plans

Dietary patterns are composed of opposing fat and carbohydrate contents but balanced in protein (Table 1). Six-weeks of meal plans were designed for five calorie levels in each diet arm. The meal plans developed included interchangeable meal options with home-prepared recipes and meal instructions. Supporting materials are provided to facilitate adherence including eating out and frozen meal options, food brand options consistent with the plan, meal planning tools and shopping lists. Educational materials were developed based on a systematic review of strategies supporting weight loss maintenance, incorporating program components (e.g. self-monitoring tools) and core competencies reinforcing weight loss behaviors. These strategies are taught to participants through the one-on-one and group sessions in order to promote high levels of dietary adherence.

**Table 1 T1:** Mean Proposed Macronutrient Composition by Diet Group

	Low Carbohydrate, High Fat	High Carbohydrate, Low Fat
Carbohydrate (%)	32	64
Fat (%)	48	16
Protein (%)	20	20

Participants are instructed to increase their physical activity by increasing steps or step equivalents to contribute to a 500 calorie deficit each day in combination with caloric restriction. Calorie goals are determined based on resting metabolic rate and energy expenditure from activity.

### Outcome Measures

#### C-Reactive Protein

Overweight, obesity and insulin resistance are associated with increases in various cells such as adipocytes, pre-adipocytes, fibroblasts, and macrophages, which release adipokines and promote inflammation [69-71]. The amount of body fat predicts inflammatory C-reactive protein (CRP) levels among adults [72]. Inflammation decreases apoptosis, increases breast cancer invasiveness and decreases prognosis [46,73]. There is convincing evidence that persistent low grade inflammation as well as chronic inflammatory diseases are associated with several cancers in humans [44]. Importantly, inflammation measured via CRP is inversely associated with breast cancer survival, even independently of BMI [36,43]. Therefore, CRP is considered the primary outcome.

### Secondary Outcomes

#### Other Markers of Inflammation

Other inflammatory cytokines that mediate the inflammatory response will also be measured, including Interleukin-6 (IL-6) and TNF-α. IL-6 has been correlated with extent of tumor invasion and metastasis [74].

### Glucose Homeostasis

As hyperglycemia and insulin resistance are associated with an increased risk for breast cancer [75], factors related to these metabolic processes will be measured including homeostasis model assessment (HOMA). HOMA is a method used to quantify insulin resistance and pancreatic beta cell function and is a calculated index based on fasting levels of insulin and glucose, giving an integrated view of glucose utilization. HOMA has been shown to be associated with increased breast cancer incidence [75], and higher breast cancer mortality in the HEAL study [76]. Fasting insulin alone has also been shown to be predictive of survival in breast cancer patients [77]. In addition, insulin-like growth factor-1 (IGF-1), IGF binding protein-3 (IGFBP-3) and the ratio of IGF-1:IGFBP-3, which provides an estimate of biologically available IGF-1, a more useful indication of overall, longer term control of glucose homeostasis in relation to breast cancer risk, will be measured [78]. Serum IGF-1 is positively associated with breast cancer risk, as well as changes in response to caloric restriction and nutritional alterations [79]. Measuring the effects of two differing dietary patterns on endogenous production of IGF-1 will help to further characterize dietary effects on breast cancer risk.

### Cellular Oxidation

The inflammatory response stimulated by obesity and insulin resistance also increases oxidative stress in the body [80]. During oxidative stress, byproducts of nucleic acid metabolism including reactive oxygen species (ROS) promote cancer development by causing genetic mutations and DNA damage [55,56,81]. Secondary measures of cellular oxidation that will be measured include 8-hydroxy-deoxy-guanosine (8-OH-dG) reflecting defects in DNA repair capacity, and markers of whole body lipid peroxidation, 8-isoprostane-F2-alpha (8-iso-PGF_2α_), which have been shown to play a role in breast carcinogenesis [49,82,83]. These byproducts of oxidation are more common in cancerous breast tissue compared to normal breast tissue [49,55,56], and may also be altered with reducing energy intake [51,52] and changes in dietary macronutrient composition [84].

### Hormone Metabolism

Overweight postmenopausal women have elevated concentrations of circulating estrogens and lower concentrations of sex hormone binding globulin (SHBG), which promotes cell growth, putting them at more than twice the risk for breast and endometrial cancers, as evidenced in the Healthy Eating and Lifestyles (HEAL) study and the European Prospective Investigation into Cancer and Nutrition (EPIC) study [12,85,86]. Adipose tissue exhibits aromatase enzyme activity, converting androgenic precursors to estradiol and estrone. Estrogens may promote tumorigenesis through direct or indirect induction of free radical-mediated DNA damage, genetic instability, cell mutations and cell proliferation. Agents such as tamoxifen (selective estrogen receptor modulators) or the aromatase inhibitors have been shown to reduce breast cancer incidence and recurrence [87]. Although warranted, there are currently no published randomized, controlled studies of the effect dietary pattern has on estrogens or SHBG and other candidate mechanisms [88-90]. Secondary hormone metabolism outcomes will include estradiol, estrone, progesterone, and SHBG.

### Adipokines

Adipose tissue produces the hormones adiponectin and leptin. Low adiponectin, which is an anti-inflammatory and insulin sensitizer, is associated with increased breast cancer mortality in breast cancer survivors [76], with leptin regulating energy balance and metabolism and playing a role in cell proliferation [91]. These adipokines, as well as plasma ghrelin, will be measured to provide biological determinants that may also help explain differences in response to the opposing dietary patterns.

### Anthropometry

Weight, height and waist and hip circumferences are measured using a standardized protocol. Participants are in their bathing or body suit for all measurements. Anthropometry is measured monthly in the intervention group and at baseline and 6 months in the control group. Height is measured with a stadiometer. Body circumferences (waist and hip circumferences) are measured using a specially manufactured, tension controlled cloth tape. The participant is instructed to stand erect with arms relaxed at their sides, feet together and abdomen relaxed. Waist circumference is defined as the diameter around the abdomen; it is measured at the midpoint between the top of the hip bone and the bottom of the rib cage. The measurement is taken at the end of a normal expiration, with the tape pulled tight but not compressing the skin. Hip circumference is measured at the level of the maximum extension of the buttocks.

### Body Fat

BOD POD technology is fundamentally the same as underwater (hydrostatic) weighing, but uses volumetric air displacement versus water displacement. All outcome measures including weight are assessed using validated and standardized measuring equipment and techniques. Air displacement plethysmography (BOD POD, Life Measurement, Inc., Concord, CA) has been shown to measure changes in body composition in response to weight change to the same extent as dual x-ray absorptiometry (DEXA), with similar sensitivity [92]. The BOD POD measures the volume of air a person's body displaced while sitting inside a comfortable chamber. By using air versus water, the BOD POD offers a fast, safe, and easy-to-use tool for measuring body composition, without sacrificing accuracy. Since it is based on the same whole-body measurement principle as hydrostatic weighing, the BOD POD first measures the subject's mass and volume. From these measurements, whole-body density is determined, and body fat and lean mass calculated using standardized equations.

### Process Measures

#### Physical Activity

Energy expenditure is measured using accelerometry and heart rate monitoring technology (Actiheart, CamNtech, Inc., Boerne, TX). The Actiheart has been assessed as being valid and reliable in predicting energy expenditure with walking and running [93,94]. Individuals are given a plan to increase physical activity to ultimately meet national guidelines (10,000 steps/d) and facilitate energy balance tailored to their individual lifestyle and physical ability.

### Dietary Adherence

There is often a large loss to follow up in lifestyle interventions, especially in longer term studies, which could cause selection bias due to attrition and over-estimation of treatment effects [95]. One method to optimize adherence and retention is to carefully select participants who are more likely to complete the study. The requirements of completing and returning the screening questionnaires, attendance at the individual meetings, the necessity of a clinic visit and the successful completion of the one week food records and other questionnaires are burdensome on potential participants and result in a lower drop-out rate after assignment to a study arm. Additionally, study coordinators stress to potential participants at every screening visit the various obligations required of them in order to take part in this very structured diet study. Potential participants with doubts about participating will be encouraged not to participate in the study or encouraged to participate in the control arm until they are more prepared to make the necessary commitments to the study. The major method for monitoring adherence to the diet is by the use of daily food record with physical activity/step records. Adherence is promoted by 1) ongoing individual contacts in person and by telephone, mail, and email; 2) continuous care/problem solving treatments; 3) skills training to prevent or cope with setbacks; 4) social support and social influence strategies and 5) ease of recording dietary intake by use of meal codes. Additionally, a program of weight management competencies with ongoing assessment and reinforcement has been developed to target the gaps in participants' knowledge and behaviors related to weight loss. During the screening process, participants will be assessed for their readiness to change or maintain change, as well as their general wellbeing or level of depression, which has been shown to be reciprocally associated with obesity and predict weight maintenance success [96].

### Monitoring Breast Cancer Recurrence

Women with a history of invasive breast cancer are seen every 3 months for the first 2 years following treatment at the study site clinic. At each visit, a clinical history is updated, a physical examination is performed by the attending oncologist, and serum levels of CA 27.29 and CEA are determined. The frequency of clinical visits decreases to every 6 months for the next three years, and follow up occurs annually thereafter. Following a patient's enrollment into this study, and for the duration over which the project is funded, at each of these clinical visits, the relevant disease recurrence data will be recorded along with height, weight, and body composition. Blood will also be drawn and banked at each visit for subsequent hypothesis testing, although such analyses are beyond the scope of this project.

### Data Analysis

All data elements collected will be examined using descriptive statistics (mean, median, SD, range, percentiles, proportion) and graphical summaries (box plots, profile plots by time and diet group). Log transformations will be made before further analysis to stabilize variances as needed.

The primary hypothesis on C-reactive protein will be tested using the following ANCOVA model:

Where Y_4 _is the outcome measure at the end of 6 months, Y_1 _is the outcome measure at baseline, and, GLYC is a 2-level indicator for dietary pattern. This method of analysis adjusts for any remaining pre-treatment differences between groups (a precaution against imbalance after diet assignment) and reduces variability in the data being analyzed [97], thus improving the power of the test for the main effect of interest, b_2_.

There will be a wealth of information in the repeated measures on each subject; the results for all measures using all available data from all time points will be estimated in a mixed-effects repeated measures model to assess the slopes and between group differences after each month of weight loss [98]. The power of this approach lies in its ability to incorporate all of the available longitudinal data even in the unbalanced case, that is, when some of the observations are missing for one or more individuals. Observations within a person over time are allowed to be correlated while observations across individuals are assumed to be independent. These models will also be used to explore the effects of breast cancer stage, BMI (a time-varying covariate) and age.

Depending on the appearance of change over time (seen in the profile plots of each outcome measure by time and diet) linear or nonlinear mixed models will be used. If the trend appears to be linear, the following model for the response vector ***y***_i _for the *i*th group will be used:(1)

where **b**_*i *_~ *N *(0,D) and **e**_*i *_~ *N *(0,R_*i*_) are independent. X_*i *_is a fixed effects design matrix that includes indicators for diet group (1, 2), assessment time (after each 1.5 kg fat loss, and potential covariates (age) or confounders (disease stage, BMI). **Z**_*i *_is a design matrix for the random effects that allows random subject deviations from the population average response. The marginal distribution of **y**_*i *_is normal with mean **X**_*i *_*β *and variance . Parameter estimation in SAS allows a wide range of specifications for the forms of **D **and **R**, and combines empirical Bayes and restricted maximum likelihood using the EM algorithm.

If the descriptive graphs suggest a nonlinear model is appropriate, we will estimate:(2)

Where **b**_*i *_~ *N *(**0**,**D**) and **e**_*i *_~ *N *(**0**,**R**_*i*_). The marginal distribution of **y**_*i *_is difficult to find in most cases, but its mean and variance can be approximated by

Where  is the partial derivative of *f *(⋅) with respect to **b**_*i*_. Parameter estimation in SAS combines a linearization algorithm, such as Gauss-Newton, and the method of Laird-Ware for linear mixed models. We will explore the use of nonlinear models only if it appears that the response trajectory of *Y *over time could be fit well by a smooth nonlinear function. Otherwise, simpler piece-wise linear mixed models will be fit using Equation 1 above.

Secondary measures in the 4 families of outcomes will be assessed using the same statistical methods described above for the primary measures. That is, ANCOVA assessment of the measure by diet group at 6 months followed by an exploratory analysis with mixed models using all available data.

Mixed models will also be used to estimate the effects of fat loss on the 4 families of outcomes. Fat loss and weight loss will be modeled with the expectation that differences across diets will be minimal, and success in weight loss better explained by age, initial BMI, and usual level of physical activity.

Missing data are expected to be missing at random, and are unlikely to exceed 5% of all observations. This assumption will be checked during the initial descriptive analysis of the data after database lock, and appropriate sensitivity analyses will be done if there is evidence that the data are MNAR (missing not-at-random) [99]. Given the nature of the patient population and the incentives to return for monthly evaluations, we expect to collect most endpoint measures regardless of compliance. We will accrue 370 subjects with the expectation of completing at least 135 per diet group and 100 in the control group, that is, 10% loss to follow-up. Analysis will be intent-to-treat. All statistical analysis will be done using SAS version 9 (SAS Institute, Cary, NC).

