## Methods/Design

### Study Design

The study, called CHOICE, is a non-randomized, controlled trial in post-menopausal breast cancer survivors investigating whether an energy restricted dietary pattern, i.e. low carbohydrate, high fat or low fat, high carbohydrate, with progressive fat loss during a weight loss program can alter the likelihood of long term survival following treatment for breast cancer as reflected in metabolic and hormonal prognostic biomarkers. A total of 370 women will be accrued and assigned to one of the two dietary intervention arms based on eating preferences or a non-intervention control arm (n = 135 to each intervention arm, n = 100 to the control arm) and followed for 6 months as illustrated in Figure 1. Anthropometric measurements are conducted and biomarkers collected at baseline and 6 months in the control arm, and monthly in the intervention arms in order to model the shape of the metabolic and hormonal response curves.

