### Study Aims

#### Primary Aim

The primary aim of the study is to investigate whether dietary pattern (low carbohydrate or low fat) alters the patterns of change observed in circulating factors involved in chronic inflammation, glucose homeostasis, cellular oxidation, and steroid hormone metabolism during progressive loss of body fat. The primary outcome measure is high sensitivity C-reactive protein. All other measurements are considered secondary endpoints.

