### Patient Recruitment (Study Setting and Participants)

CHOICE recruits women who have been treated for breast cancer and attend Rocky Mountain Cancer Centers in Denver, CO, USA. There are approximately 2000 women enrolled in the clinic. Clinic physicians refer breast cancer survivors who meet the eligibility criteria. Participants are also recruited by way of study flyers and brochures posted throughout the clinical facility. Written informed consent is given by subjects when they choose to participate in the program. Following informed consent, participants complete questionnaires that provide demographic, lifestyle and clinical data including age, marital status, ethnicity, level of education, household income, medical history, medicine and supplement use, PAR-Q (Physical Activity Readiness Questionnaire), and emotional well-being. Participants are also interviewed regarding their dieting, weight history and readiness for engaging in a comprehensive weight loss program. This population has a mean age of 60; they are > 98% white and over 50% have post baccalaureate training. While not representative of the general population, this population has proven a very high compliance rate in previous diet-cancer studies conducted by our laboratory [57,65,66].

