### Limitations

Limitations include the fact that the study is neither double blinded nor randomized; results may not be generalizable. The population is free living and as such is subject to issues of compliance and difficulties with quantifying dietary intake and physical activity.

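### Diet arm follows eating preference, but the primary CRP model adjusts only for baseline CRP, so confounding can pass into the diet effect

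*Protocol article*

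**What the plan says.** - **Assignment.** Study Design says the study "is a non-randomized, controlled trial in post-menopausal breast cancer survivors", with women "assigned to one of the two dietary intervention arms based on eating preferences or a non-intervention control arm". Planned sizes are "n = 135 to each intervention arm, n = 100 to the control arm".
- **Primary outcome.** Primary Aim: "The primary outcome measure is high sensitivity C-reactive protein".
- **Primary model.** Data Analysis defines three terms for the ANCOVA: the 6-month value (Y_4), the baseline value (Y_1) and a two-level diet indicator (GLYC). The effect of interest is b_2. No other covariate is described.
- **Claim made for the model.** "This method of analysis adjusts for any remaining pre-treatment differences between groups (a precaution against imbalance after diet assignment".
- **Other covariates.** Data Analysis brings stage, BMI (as a time-varying covariate) and age into the mixed models in order to explore their effects. The description of the design matrix there labels stage and BMI as confounders. For secondary measures, said to use the same methods as the primary, the mixed-model step after the ANCOVA is called exploratory.
- **Limitation.** Limitations says "the study is neither double blinded nor randomized; results may not be generalizable".

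**The concern.** The sentence about pre-treatment differences uses the reasoning of a randomised trial. After randomisation, baseline imbalance is due to chance, and adjusting for the baseline outcome mainly buys precision. Here a characteristic of the woman decides the arm, so the arms may differ systematically in whatever goes with food preference. A one-covariate model does not deal with that.

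The document itself gives reason to expect that such differences matter. The C-Reactive Protein section says body fat predicts CRP. Data Analysis expects success in weight loss to depend on age, initial BMI and usual activity. None of these is in the primary model. If the two preference groups differ on them, part of that difference can be reported as an effect of macronutrient composition on CRP. Describing the analysis as intent-to-treat does not help, because analysing by assigned arm preserves only the comparability that assignment created.

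**Working it through.** **1. Model terms against the assignment rule.** The document states no alpha, power, effect size or SD for CRP, so there is no planned figure to reproduce. The arm sizes add up: 135 + 135 + 100 = 370. The check is therefore one of logic.

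- The terms listed imply Y_4 = b_0 + b_1·Y_1 + b_2·GLYC. The displayed equation is not legible in the text reviewed. This form rests on the terms defined with it and on the label b_2 for diet.
- Take a baseline characteristic U, scaled to SD 1, that differs between the arms by d. Let it have effect g on Y_4 given Y_1, and within-arm correlation r with Y_1 (also SD 1), with the arm gap in Y_1 arising only through U.
- Adjusting for Y_1 leaves a gap in U of d − r·(r·d) = d(1 − r²). The bias in b_2 is then g·d·(1 − r²).
- So baseline CRP absorbs the share r² of the gap. The bias vanishes only if U is balanced, has no effect given baseline CRP, or is fully carried by baseline CRP.

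**2. Size of false-positive inflation (illustration).** Assumptions, none of them from the document: two-sided 0.05, no true diet effect, and bias B in residual SD units. The number per arm is 135, or about 122 after the 10% loss mentioned in Data Analysis (135 × 0.9 = 121.5). With SE = √(2/n), the rejection rate is Φ(B/SE − 1.96) + Φ(−B/SE − 1.96).

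| n per arm | SE | B = 0.1 | B = 0.2 |
|---|---|---|---|
| 135 | √(2/135) = 0.122 | 13.0% | 37.6% |
| 122 | √(2/122) = 0.128 | 12.2% | 34.6% |

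**3. Does adding the covariate help?** Simulation with 4,000 replicates and 135 per arm, no true diet effect, assuming r = 0.3, a slope of 0.6 on Y_1 and residual SD 0.7. Bias is in units of the SD of Y_1.

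| d | g | Bias by formula (1 − r² = 0.91) | Simulated bias, baseline-only | Rejection, baseline-only | Rejection with U added |
|---|---|---|---|---|---|
| 0.3 | 0.2 | 0.055 | 0.056 | 9.6% | 4.8% |
| 0.3 | 0.3 | 0.082 | 0.083 | 14.1% | 4.6% |
| 0.5 | 0.2 | 0.091 | 0.095 | 18.1% | 4.9% |
| 0.5 | 0.3 | 0.137 | 0.138 | 32.0% | 4.8% |

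Divided by 0.7, the formula biases run from about 0.08 to 0.20 residual SD, close to the range in step 2. Where U was balanced or had no effect, both models rejected in 4.6% to 5.9% of replicates.

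**4. Could the mixed models stand in for the primary adjustment?** They are fitted to all measures, CRP included, and may contain age, stage and BMI. But they follow the primary test and do not replace it. BMI there is updated over time, so it partly lies after the diets start and may carry some of the diet effect. That is not adjustment for baseline BMI.

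**The case against.** Several points on the other side are fair.

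- **Confounding is not ignored.** The plan names stage and BMI as confounders and lists the absence of randomisation as a limitation. This stands. The criticism is narrower: those covariates do not reach the primary test, and the limitation is framed only as generalisability.
- **Eligibility narrows the differences.** Both diet arms come from one clinic, with BMI limited to 25 to 34.9 and tobacco users, women treated for diabetes and women on restrictive diets excluded. They share one activity protocol. This makes large gaps less likely, and nothing in the document shows that gaps as large as those assumed above will occur.
- **Detail belongs in the analysis plan.** An exact covariate list could be left there. But the article fixes the terms of the primary model and makes a claim for it, and that claim is wrong as written.

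Stronger readings are tempting and should be resisted. A reader might infer that the plan claims to remove all pre-treatment differences; it says it adjusts for them. A reader might infer that confounding enters the diet effect in full; baseline CRP absorbs part of it. A reader might also add the effect of measurement error in a single baseline CRP value. That is a separate matter: the document gives no reliability for CRP, and adding covariates does not directly correct it.

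**Conclusion.** The point holds. Under preference-based assignment, an ANCOVA with baseline CRP as its only covariate does not adjust for any remaining pre-treatment difference, and following the plan as written can give a confounded primary diet effect. The confounders the plan itself names are absent from the primary model.

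The size and direction of the bias are unknown. The range of roughly 12% to 38% false positives is conditional on assumed residual confounding of 0.1 to 0.2 residual SD, a two-sided 0.05 test, 122 to 135 women per arm and no true diet effect. It shows how sensitive the test is to modest bias; it does not estimate this trial's error rate.

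**What to change.** 1. Pre-specify in the primary ANCOVA a short set of baseline covariates: age, disease stage, baseline BMI or percent body fat, type of adjuvant therapy, relevant medicine use and baseline activity. All are already collected. Patient Recruitment covers age and "level of education, household income, medical history, medicine and supplement use"; Eligibility covers stage, adjuvant therapy and accelerometry at the start; Study Design and Body Fat cover body size and composition.
2. Keep habitual fat and carbohydrate intake (from the screening food records) and propensity-score weighting for sensitivity analyses, with overlap checked. Habitual intake may strongly predict a preference-based choice, so forcing it into the primary model could cost overlap and precision.
3. Replace the sentence in Data Analysis with: *adjusts for the measured baseline value of the outcome and the listed covariates*.
4. State residual confounding in Limitations, and report the diet contrast as an adjusted association.

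Cost: with about 121.5 completers per arm, 2 × 121.5 − 3 = 240 residual degrees of freedom are available. Because stage and therapy type have several levels, the list uses about 10 or slightly more. The rest is wording and a little programming, with no new data. Unmeasured confounding would remain, which is why item 4 is needed as well.

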### Eligibility

Participants must be referred by their clinical oncologist, have a pathology report confirming the resected stage of breast cancer and documentation of the type of systemic adjuvant therapy, as well as have a BMI in the overweight or obese class I range (BMI 25-34.9 kg/m^2^). Eligible participants: must be at least 4 months post radiation or chemotherapy treatment for breast cancer with no evidence of metastatic disease; must not anticipate having surgery over the study duration period; must not follow a special diet excluding foods or food groups; have not lost 2 or more kg of body weight over the month preceding study initiation; must not be taking pharmaceuticals or supplements for weight management; are not being treated for diabetes or blood glucose control; have no history of eating disorders; do not have digestive issues that may interfere with dietary intake, such as irritable bowel syndrome, Crohn's disease, or diverticulitis; have never had surgery involving constriction or removal of any portion of the gastrointestinal tract; have not been diagnosed with hepatitis B, C, or HIV; do not have implanted electronic devices such as a pacemaker; and do not use tobacco products. Participants must also be willing to follow a dietary plan prescribed for the duration of the study; adhere to American Cancer Society alcohol guidelines (≤ 1 standard drink per day); maintain or increase physical activity as prescribed to achieve negative energy balance required for 0.5-1.0 kg weight loss per week; wear a pedometer and record daily activity; wear an accelerometer/heart rate monitor for 2 weeks during the study (1 week at the beginning and 1 week at the end of the study); wear a body or swim suit and cap for body composition testing; record food intake daily; and attend up to ten one-on-one clinic visits and 5 group visits with seven fasting blood and first-void urine samples in the intervention groups, or three one-on-one clinic visits and two fasting blood and first-void urine samples in the control group over 26 weeks.

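### The estradiol, estrone, progesterone and SHBG models leave out endocrine therapy, although aromatase inhibitor users can enrol and the protocol's own route from body fat to estrogen is aromatase

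*Protocol article*

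**What the plan says.** The Hormone Metabolism section lists the outcomes: "Secondary hormone metabolism outcomes will include estradiol, estrone, progesterone, and SHBG". Under Data Analysis, "Secondary measures in the 4 families of outcomes will be assessed using the same statistical methods described above for the primary measures", so these four markers are analysed as CRP is.

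The CRP plan has two parts:

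- **ANCOVA at 6 months.** The baseline term "is the outcome measure at baseline, and, GLYC is a 2-level indicator for dietary pattern". No other covariate is named.
- **Mixed models on all time points.** The fixed effects include diet group, assessment time and "potential covariates (age) or confounders (disease stage, BMI". The text adds: "These models will also be used to explore the effects of breast cancer stage, BMI (a time-varying covariate) and age". Mixed models are also to estimate the effect of fat loss on all four outcome families.

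On treatment history, Eligibility says participants "must be at least 4 months post radiation or chemotherapy treatment for breast cancer with no evidence of metastatic disease", and it requires "documentation of the type of systemic adjuvant therapy". It neither excludes nor requires current endocrine therapy. The Patient Recruitment section adds a questionnaire, completed after consent, that covers medicine use.

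The Hormone Metabolism section gives the pathway: "Adipose tissue exhibits aromatase enzyme activity, converting androgenic precursors to estradiol and estrone". It then names tamoxifen, as a selective estrogen receptor modulator, and the aromatase inhibitors.

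**The concern.** The biological reason for expecting fat loss to lower estradiol and estrone is aromatase in fat tissue. An aromatase inhibitor acts on that same step. The protocol's own rationale therefore predicts a different estrogen response to fat loss in inhibitor users, and the stated models average over users and non-users.

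Two readings of the results are at stake.

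- **Secondary Aim 1** compares how the metabolic, inflammatory and oxidation markers change with fat loss against how the sex steroids change. If medication flattens only the steroid curve, the aim could report dissimilar patterns that owe something to drug use rather than to biology.
- **The diet comparison of hormones** is exposed because women are assigned by eating preference, not at random. The mix of endocrine therapy may differ between arms. For tamoxifen users, and for SHBG and progesterone, this confounding and plain heterogeneity are the relevant worries; the aromatase argument does not reach them.

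**Working it through.** **Plan's own figure.** There is none to reproduce. The article gives no alpha, power, effect size or SD for any hormone outcome, no share of women on endocrine therapy, and no residual estrogen response in users. The arithmetic below is an illustration.

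**Is the modifier handled elsewhere?** Adjusting for the baseline value, and random subject effects, absorb much of a stable difference in level between users and non-users. They do not absorb a difference in response to fat loss, or a therapy started, stopped or switched during the 6 months. Disease stage is not therapy type.

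**Inputs.** From the article: 135 women per diet arm. Assumed:

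- two-sided alpha 0.05;
- an effect that would have 80% power if no woman used an inhibitor, which is (1.960 + 0.842) × √(2/135) = 0.341 SD;
- equal residual variance, and the same share p of users in each arm;
- users keep a fraction r of the non-user effect.

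**Formulas.**

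- Pooled effect as a fraction of the non-user effect: 1 − p + pr
- Pooled power: Φ(2.802 × (1 − p + pr) − 1.960)
- Power in non-users alone: Φ(2.802 × √(1 − p) − 1.960)

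| p | Pooled fraction, r = 0 | Pooled power, r = 0 | Pooled fraction, r = 0.5 | Pooled power, r = 0.5 | Non-users alone |
|---|---|---|---|---|---|
| 0.3 | 0.70 | 50% | 0.85 | 66% | 65% |
| 0.5 | 0.50 | 29% | 0.75 | 56% | 51% |
| 0.7 | 0.30 | 13% | 0.65 | 44% | 34% |

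For example, at p = 0.5 and r = 0.5: 2.802 × 0.75 − 1.960 = 0.14, and Φ(0.14) = 56%.

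**Break-even.** Pooling has more power than non-users alone when 1 − p + pr > √(1 − p), that is, when r > (√(1 − p) − (1 − p))/p:

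- p = 0.3: (0.837 − 0.700)/0.3 = 0.46
- p = 0.5: (0.707 − 0.500)/0.5 = 0.41
- p = 0.7: (0.548 − 0.300)/0.7 = 0.35

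**Fat-loss slope.** A simulation used 270 women and 2000 runs, with all parameters assumed: slope −0.030 per kg of fat on a log scale in non-users and zero in users, with users' hormone level 1.5 log units lower. The baseline-adjusted model without therapy gave mean slopes of −0.021, −0.015 and −0.009 at p = 0.3, 0.5 and 0.7. With therapy and its interaction with fat loss added, the non-user slope came back at −0.030 each time. Power for a non-zero slope was 69%, 44% and 18% without those terms, and 85%, 73% and 52% for the non-user slope with them. These gains depend on the zero response assumed in users.

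**The case against.** The strongest reply is that the covariate list is not closed. The mixed-model text speaks of potential covariates, these models are exploratory for secondary outcomes, and a condensed article may leave marker-specific covariates to a fuller document. Recording therapy leaves room to use it later. This stands in part: nothing forbids the term. But the article does fix one model for all four families and does name its confounders, and the variable most specific to the hormone family is not among them.

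A reader might go further and infer that the estrogen signal is diluted by a known amount because users cannot respond at all. The documents do not support that. They give no degree of suppression, so zero response is an assumption, and log transformation is allowed, so proportional change may be the relevant scale.

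A reader might also extend dilution to tamoxifen, or to SHBG and progesterone. The article describes tamoxifen as a receptor modulator, and its aromatase statement covers only estradiol and estrone.

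A third tempting step is to make women off inhibitors the main estrogen result. That changes the question from the enrolled survivors to a subgroup. By the break-even above, it also loses power once users keep roughly 35% to 46% of the effect.

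Finally, baseline adjustment does deal with much of any imbalance in hormone level between arms. What it leaves is the difference in response.

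**Conclusion.** The point holds in a limited form. As written, the estradiol and estrone analyses average over an effect modifier that the protocol's own mechanism predicts, and the stated adjustments do not remove it. The likely direction is dilution of the fat-loss effect, with a possible false contrast between families in Secondary Aim 1. For tamoxifen, SHBG and progesterone, only heterogeneity or confounding between preference-based arms is at issue.

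The size cannot be derived from the article. Over assumed shares of 30% to 70%, the pooled effect is 70% to 30% of the non-user effect if users do not respond, and 85% to 65% if they keep half the response. These figures also rest on equal variance and the same share of users in each arm. The outcomes are secondary, and the primary CRP test is not in question.

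**What to change.** In the estradiol, estrone, progesterone and SHBG models:

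- Add baseline endocrine therapy (none / tamoxifen / aromatase inhibitor) as a covariate, taken from the documented adjuvant therapy and the medicine-use questionnaire.
- Add its interaction with fat loss and with diet group.
- Report the estradiol and estrone effects by aromatase inhibitor use alongside the pooled estimate. Keep the pooled estimate in place; do not make the non-user subgroup the main result.
- Read the Secondary Aim 1 comparison with both sets of results in view.
- Account for changes of therapy during the 6 months only where they are recorded. The article does not say that medication is recorded again after baseline.

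The baseline part uses information already collected. The cost is a few extra model terms, and stratum-specific estimates that are less precise than the pooled one, all within secondary analyses.
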